### Eligibility criteria {10}

Inclusion criteria for participants are.Minimum age 18 yearsMaximum age 60 yearsOutpatients with at least four diagnostic criteria of BPD fulfilled according to the structured clinical interview International Personality Disorder Examination (IPDE based on DSM-5) [28].Overt aggression based on OAS-M (sum of items 1–3) ≥ 15 and irritability based on OAS-M (sum of items 5–6) ≥ 6 within two weeks prior to study inclusionLiving within 70 km of a study center or within easy reach of a study centerSufficient knowledge of German for participation in group therapy

Exclusion criteria for participants are.Suicidality (assessed on an individual basis by a clinician after positive screening on OAS-M)Acute/previous schizophrenia (assessed on an individual basis by a clinician after positive screening on MINI-DIPS)Acute bipolar I disorder assessed on an individual basis by a clinician after positive screening on MINI-DIPS)Acute moderate to severe substance use disorderAutism Spectrum Disorder assessed on an individual basis by a clinician after positive screening on AQ-10No ability or willingness to abstain from drug or alcohol use during therapy sessions (assessed by a clinician on an individual basis)History of a serious medical condition that interferes with participation in regular therapy sessionsSevere cognitive impairment (IQ < 70) assessed on an individual basis by a clinician after positive screening on mini-qOther ongoing psychotherapyIncrease in current psychotropic medication or initiation of new psychotropic medication within two weeks prior to study assignment (6 weeks instead of 2 weeks for fluoxetine)Ongoing criminal investigation, placement in a forensic hospital or incarceration for more than 2 years

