**Table 1 Tab1:**
[figure not shown]
Overview of the study procedure and the assessments and collection of outcomes

IPDE (International Personality Disorder Examination for DMS-5): Suitability and assignment; MINI-DIPS for the assessment of exclusion criteria: Schizophrenia (lifetime), Bipolar I disorder (current), moderate and severe substance use disorder, and comorbidities; LHA (Life History of Aggression); mini-q: Assessment of verbal intelligence; ZAN-BPD (Zanarini Rating Scale for Borderline Personality Disorder): Measure of symptom severity; OAS-M (Overt Aggression Scale-modified): Interview-based measure of the frequency and severity of overt aggressive behavior that has occurred in a 2-week period; Items 1-3: verbal aggression, aggression against objects, aggression against others; Item 4: Aggression against oneself; Items 5–6: Irritability, subjective and visible from the outside; Suicidality: measured with item 7 and reviewed by a diagnostician with clinical expertise on an individual basis; ARS, Anger Rumination Scale; BIS-15, Barratt Impulsiveness Scale; BSCL-53, Brief-Symptom-Checklist; CAMSQ, Certainty About Mental States Questionnaire; CTQ, Childhood Trauma Questionnaire; DERS-36, Difficulties in Emotion Regulation Scale; EmpaToM, Empathy and Theory of Mind paradigm; ERC Emotion Classification task; GLAT Grid Learning Aggression Task; MEQ-16, Mentalizing Emotions Questionnaire; PDS-ICD-11, Personality Disorder Severity Scale; PD-T, Participation-related Documentation, Therapist Version; PD-P, Particpantion-related Documentation, Patient Version; PID-5-BF+M, Personality Inventory for DSM-5; RSQ-20, Rejection Sensitivity Questionnaire; SNQ, Social Network Questionnaire; SOFAS, Social and Occupational Functioning Assessment Scale; Soc.-Dem., Sociodemographic Questionnaire; STAXI-II, State-Trait-Anger-Inventory II; UCLA-3 Loneliness Assessment; WHOQoL-BREF, WHO Quality of Life; NEQ, Negative Events Questionnaire; GQ-D, Group Questionnaire, German Version

Note: Each shade corresponds to a specific phase or time point to help differentiate study phases over time. The assessment of the primary outcome is highlighted in black for easy identification

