### Methods for additional analyses (e.g. subgroup analyses) {20b}

Exploratory outcomes and endpoints for mediation analyses will be analyzed analogous to the primary outcome for continuous variables and using logistic mixed-effects models for binary variables. Safety data will be analyzed descriptively with lists of (S)AEs by treatment arm. To date, to the best of our knowledge, there is no evidence of gender-specific treatment effects in BPD. As men with BPD have often been neglected in BPD research [21], we plan an exploratory subgroup analysis by gender.

Data not relating to primary or secondary outcomes (e.g., baseline patient characteristics, safety data, or therapist adherence data) may be analyzed and published before the study is completed, as long as these analyses do not affect the interpretation of the primary or secondary outcomes. Such early analysis will be conducted with appropriate caution to ensure that it does not interfere with the integrity or the statistical power of the final results.

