### Adverse event reporting and harms {22}

There are no direct risks to patients participating in this study. All patients and one of the two group therapists fill out a participation-related documentation after each therapy session, including questions about acute suicidality. Patients also have the option of a brief crisis intervention with one of the two group therapists. Potential SAEs are defined as patient death, acute mental illness requiring hospitalization, acute suicidality, and acute aggression. Potential AEs are defined as delinquency or threat of violence, serious physical illness, serious accident, and new-onset acute mental disorder (comorbid with borderline personality disorder). The study collects, assesses, and manages AEs and SAEs, as well as any unintended effects related to the study interventions or their administration. AEs and SAEs are recorded; SAEs are reported to the chief principal investigator within 24 h, and then reported to the DSMB. To this end, the occurrence of SAEs is categorized, and their severity, relationship to study interventions, and outcome are systematically assessed and documented in the eCRF. Appropriate follow-up actions will be taken for all SAEs in consultation with the DSMB. The DSMB will advise whether the trial should be continued or stopped if a cluster of SAEs is suspected. These decisions will be based on ongoing risk assessments and careful evaluation of the available safety data. Periodic reviews are performed and results are reported to the ethics committees as required.

Any patient showing signs of acute suicidality or severe aggression requiring immediate crisis intervention will be referred to specialized facilities while continuing their randomized treatment, provided that the crisis intervention does not exceed 14 days. In cases of violence, either during therapy sessions or in life-threatening circumstances outside of therapy, therapy will be discontinued and the participant will be referred to appropriate care, either inpatient or outpatient.

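### The adverse event definition admits a mental disorder only if it is new, so worsening of existing illness short of a listed serious event stays out of the by-arm safety lists

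*Protocol article*

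**What the plan says.** The definitions are in the protocol article under Adverse event reporting and harms {22}. For adverse events: "Potential AEs are defined as delinquency or threat of violence, serious physical illness, serious accident, and new-onset acute mental disorder". The sentence then qualifies the last item as a disorder comorbid with borderline personality disorder. For serious adverse events: "Potential SAEs are defined as patient death, acute mental illness requiring hospitalization, acute suicidality, and acute aggression". The section says the trial also collects AEs and SAEs "as well as any unintended effects related to the study interventions or their administration". It describes further assessment for serious events: "the occurrence of SAEs is categorized, and their severity, relationship to study interventions, and outcome are systematically assessed and documented in the eCRF".

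The analysis is in Methods for additional analyses {20b}: "Safety data will be analyzed descriptively with lists of (S)AEs by treatment arm".

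Three other places bear on the point:
- Eligibility criteria {10} requires at least four diagnostic criteria of BPD and "Overt aggression based on OAS-M (sum of items 1–3) ≥ 15" within two weeks before inclusion. Suicidality is an exclusion criterion.
- The Table 1 legend says the MINI-DIPS covers exclusion diagnoses, including "moderate and severe substance use disorder, and comorbidities". It describes OAS-M items 1–3 as verbal aggression and aggression against objects and against others.
- Outcomes {12} makes the same three OAS-M items, 24 weeks after treatment, the primary outcome.

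**The concern.** Deterioration of an illness the patient already has is an obvious harm to look for in a psychotherapy trial. Here the whole sample has such an illness by design, and comorbidities are documented before randomization. An AE definition that admits a mental disorder only when it is new excludes that deterioration unless it reaches the level of a listed serious event. If one arm made more patients moderately worse, the safety lists by arm would not show it.

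A second, smaller issue concerns interpretation. Patients are selected for aggressive behaviour, the treatment aims to reduce it, and threat of violence is counted as an AE with no stated threshold. If the treatment works, fewer such events are expected in the MAAP arm for that reason alone. A reader of the AE list could take this for a separate safety advantage.

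**Working it through.** No figure in the plan is disputed and no arithmetic applies. The check applies the stated definitions to the kinds of event that can occur.

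| Event after the start of treatment | Listed AE? | Listed SAE? | In the (S)AE lists? |
|---|---|---|---|
| New acute comorbid disorder, no hospitalization | Yes (new-onset) | No | Yes |
| Existing mental illness worsens acutely, hospitalization needed | No | Yes (no new-onset limit) | Yes |
| Existing illness worsens with acute suicidality or acute aggression | No | Yes | Yes |
| BPD, or a comorbidity recorded at T-1, worsens with none of these | No | No | No |
| Threat of violence, whatever the patient's level before treatment | Yes | Not by itself | Yes |

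**Fourth row.** Such a patient appears in the lists only if another listed event also happens, such as an accident or delinquency. The worsening itself is not listed. BPD worsening is excluded twice: it is not new, and the AE item refers to disorders comorbid with BPD.

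Three other provisions might fill the gap:
1. The clause on unintended effects requires a judgement that the effect is related to the intervention. It gives no criterion and is not said to feed the lists in {20b}.
2. The Negative Effects Questionnaire and the BSCL-53 are exploratory outcomes under Outcomes {12}. Neither is tied to the (S)AE lists.
3. ZAN-BPD, attacks against self and suicidality are secondary outcomes. For continuous scores, Statistical methods {20a} plans mean contrasts between arms. A mean can improve in an arm where a minority clearly deteriorates.

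**Fifth row.** Entry requires a sum of at least 15 on OAS-M items 1–3, which include verbal aggression and aggression against others. The same sum is the primary outcome. The AE category has no threshold that separates it from this behaviour. Its count by arm therefore carries part of the treatment effect. Death, physical illness and accident are not affected in this way.

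**Data available for a remedy.** Plans for assessment {18a} has OAS-M and ZAN-BPD collected at T0 and again at T1, with OAS-M at T2–T4. Outcomes {12} has both at 24 weeks. The OAS-M is interview-based, and Who will be blinded {17a} says the outcome assessors are blinded.

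**The case against.** The strongest reply is that harm is captured more widely than the AE sentence suggests. Hospitalized worsening is an SAE whether or not the illness is new. Acute suicidality and acute aggression are SAEs. Unintended effects are collected, and several symptom scales are compared by arm. The article condenses a fuller protocol, and the word potential may mean that the list is illustrative. Most of this is correct and limits the point, but it does not remove it. The restriction to new onset is a rule stated in the article, not a detail left to another document, and none of the other provisions puts non-hospitalized worsening into the lists.

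A reader might infer more than the documents support:
- *That the definitions lack any baseline reference.* New-onset is one, and since suicidality is an entry exclusion, acute suicidality is in effect a change from entry.
- *That the lists omit deterioration altogether.* The second and third rows of the table show otherwise.
- *That the SAE of acute aggression is simply the enrolment behaviour, so that the DSMB would see little but the underlying disorder.* Criteria for discontinuing {11b} and the harms section speak of serious or severe aggression needing immediate crisis intervention. That reads as a crisis-level event, and severity and relationship are assessed for SAEs.
- *That a spurious AE difference can be computed from the planned effect size of 0.55.* That figure was planned for the follow-up score, from a pilot effect on a log scale. Turning it into event counts needs a trigger rate that the documents do not give.
- *That violence-related events should count only if worse than at T0.* Threats to others are harms in themselves, and randomized arms can be compared on absolute counts. Site coordinators report events, and Implementation {16c} has allocation carried out by the coordinator or another unblinded staff member. A worse-than-baseline filter would add unblinded judgement and could leave real threats unrecorded.

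**Conclusion.** The point holds in a limited form. Worsening of BPD, or of a comorbidity recorded at T-1, that does not lead to hospitalization, acute suicidality or acute aggression meets neither the AE nor the SAE definition and is absent from the by-arm lists. Arm differences in threat of violence partly reflect efficacy and should be interpreted that way.

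The size cannot be given as a rate, because the documents contain no figure for non-hospitalized worsening or for threats of violence. The scope is clear: all 186 planned patients have BPD or subthreshold BPD, so any of them could deteriorate in the way the definition excludes.

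The conclusion assumes that sites apply the published definitions as written. If the full protocol already treats worsening as an AE, the article should say so. The primary efficacy analysis is not affected. This is an inexpensive improvement to harm detection, not a flaw that undermines the trial.

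**What to change.** 1. In Adverse event reporting and harms {22}, replace the new-onset item with: *new-onset or clinically worsened mental disorder (relative to the T-1/T0 record)*. State that this includes BPD itself, since the present qualifier refers to comorbid disorders only.
2. In Methods for additional analyses {20b}, add a descriptive table by arm of the proportion of patients whose OAS-M overt aggression score, and whose ZAN-BPD score, is worse than at T0. Give the number assessed at each visit, because the plan expects up to 30% loss to follow-up.
3. Keep recording all violence-related events regardless of baseline level. Add a sentence to {20b} that arm differences in threat of violence overlap with the primary outcome and will be interpreted in that light.

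**Cost.** A wording change, a note to sites, one extra table and some additional AE reports. Trial status gives first enrolment in May 2024 and last patient out in November 2026, so the definition would change while the trial is running, and AE counts before and after the change would not be fully comparable. Clinical worsening also calls for judgement by site staff who may know the allocation. The table offsets both drawbacks in part: it uses data already collected and applies one rule to every patient with a follow-up score. It covers aggression and BPD severity only, so worsening of other comorbid disorders depends on the revised definition.

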The secondary objectives, leading to eight secondary hypotheses, include further indicators of the hypothesized superiority of MAAP over NSSP. First, it is hypothesized that patients in the MAAP condition will show a significantly greater reduction in overt aggressive behavior (OAS-M) immediately after the intervention (T1) and/or at follow-up measurements 4 weeks (T2), 12 weeks (T3), and 20 weeks (T4) after the intervention compared to patients in the NSSP condition and as measured at baseline. Second, it is hypothesized that patients in the MAAP condition will show a significantly greater reduction in auto-aggressive behavior (OAS-M) and/or irritability (OAS-M) at T1 and/or at follow-up measurements T2–T5 compared to patients in the NSSP condition and as measured at baseline. Third, it is hypothesized that patients in the MAAP condition will show a significantly higher response rate (with response being defined as reduction of the OAS-M overt aggression score by at least 50% from baseline) at T1 and at all follow-up measurements (T2–T5) compared to patients in the NSSP condition. Fourth, it is hypothesized that after 24 weeks of follow-up, patients in the MAAP condition will show a significantly greater reduction in anger experience (STAXI-II) and aggressive behavior (3 additional items), as measured via EMA (8 assessments/day) over 2 weeks, than patients in the NSSP condition and as measured at baseline. Fifth, it is hypothesized that patients in the MAAP condition will show a significantly greater reduction in BPD symptom severity (ZAN-BPD) at T1, T3, and at T5 compared to patients in the NSSP condition and as measured at baseline. Sixth, it is hypothesized that patients in the MAAP condition will show a significantly greater reduction in trait anger (STAXI-II) at T1, T4, and T5 compared to patients in the NSSP condition and as measured at baseline. Seventh, it is hypothesized that patients in the MAAP condition will show a significantly greater improvement in everyday functioning (SOFAS) at T1, T2, and T5 compared to patients in the NSSP condition and as measured at baseline. Eighth, it is hypothesized that patients in the MAAP condition will show a significantly greater improvement in quality of life (WHO-QoL-Bref) at T1, T3, and T5 compared to patients in the NSSP condition and as measured at baseline.

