### Interim analyses {21b}

There are no formal discontinuation criteria or stopping rules for the overall trial, as no serious health risks are expected. The intervention is considered low-risk, and similar study designs conducted by our group in the past have not resulted in any complications. In particular, a previous feasibility trial using the same interventions and procedures did not raise any safety concerns. Accordingly, no interim analyses are planned. This trial is intended to run to completion unless unexpected safety concerns arise.

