### Composition of the data monitoring committee, its role and reporting structure {21a}

This trial has a Data Safety Monitoring Board (DSMB), an independent group of experts in psychiatry, clinical research, and patient safety who are responsible for ensuring patient safety throughout the trial. The primary responsibility of the DSMB is to ensure that the trial is conducted in accordance with the protocol, applicable regulatory requirements, and ethical guidelines, and that the safety of the participants is protected. The DSMB monitors (serious) adverse events (AEs and SAEs) and ensures that the trial is conducted according to safety standards. It provides strategic guidance on the progress of the trial, addresses any issues that arise during the trial, and makes recommendations for adjustments as necessary. The DSMB meets semi-annually with the sponsor and the central study coordinator to review safety data and recruitment and to make recommendations. In addition, the KKS provides data management support for this trial and oversees the scientific and ethical integrity of the trial. KKS monitoring is conducted at study initiation and annually at each participating site to ensure that the trial is following the protocol and regulatory requirements and to review progress, data safety and any emerging concerns.

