### Frequency and plans for auditing trial conduct {23}

In accordance with Good Clinical Practice (GCP) standards, trial conduct is subject to multiple levels of monitoring and oversight to ensure compliance with the protocol, regulatory requirements, and ethical guidelines. The Trial Steering Committee and the DSMB (representing the independent Data Monitoring Committee) convene every six months to evaluate the overall conduct of the trial, review accumulated data, and monitor for any potential safety or protocol adherence issues. In addition, independent monitoring is conducted annually by the KKS. These audits are performed in accordance with ICH-GCP guidelines and the KKS Standard Operating Procedures (SOPs). The KKS conducts on-site visits once per year at each site, with the option for remote video monitoring if needed. These audits cover documentation of informed consent, participant data, administration of interventions, and reporting of (S)AEs. All monitoring reports are subject to quality control by the KKS and are forwarded to the coordinating site for review and, if necessary, action. Given the low-risk nature of the intervention, no additional ethics committee meetings are conducted beyond the initial ethics approval and oversight provided by the institutional review boards. The combination of DSMB oversight and KKS monitoring ensures that participant safety, data integrity, and regulatory compliance are maintained throughout the trial.

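### The AE and SAE definitions leave out self-injury, so the harms report by arm can omit it even though OAS-M item 4 is measured as an efficacy outcome

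*Protocol article*

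**What the plan says.** The protocol article, Adverse event reporting and harms {22}, sets both event classes by enumeration. For serious events: "Potential SAEs are defined as patient death, acute mental illness requiring hospitalization, acute suicidality, and acute aggression". For the rest: "Potential AEs are defined as delinquency or threat of violence, serious physical illness, serious accident, and new-onset acute mental disorder". For serious events it adds that "the occurrence of SAEs is categorized, and their severity, relationship to study interventions, and outcome are systematically assessed". It also provides for collecting unintended effects that are related to the interventions.

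The analysis is fixed in Methods for additional analyses {20b}: "Safety data will be analyzed descriptively with lists of (S)AEs by treatment arm".

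Self-directed aggression appears elsewhere, as an outcome. Objectives {7} hypothesizes for MAAP a "significantly greater reduction in auto-aggressive behavior (OAS-M) and/or irritability (OAS-M) at T1 and/or at follow-up measurements T2–T5". Outcomes {12} lists OAS-M item 4 at 24 weeks among the secondary outcomes. Statistical methods {20a} has continuous secondary outcomes analysed like the primary one, by a mixed model with marginal means and standardized differences.

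On oversight, section {21a} states: "The DSMB meets semi-annually with the sponsor and the central study coordinator to review safety data and recruitment and to make recommendations". Section {23} has the steering committee and DSMB "review accumulated data, and monitor for any potential safety or protocol adherence issues". Section {21b} states that "no interim analyses are planned".

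**The concern.** Background and rationale {6a} describes self-injury as common in these patients, so worsening in either arm is foreseeable. An event of non-suicidal self-injury that does not lead to psychiatric admission fits none of the eight listed categories, unless a site stretches one of them. Since the safety analysis consists of lists of those categories, the harms table by arm can omit such events.

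The efficacy analysis of item 4 does not fill the gap. It estimates a difference in means and does not report how many patients got worse. The 50% response definition in Outcomes {12} applies to items 1 to 3 only and counts improvement. At stake is the completeness of the harms report, not the test of the primary hypothesis.

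**Working it through.** No figure in the plan needs reproducing here. The check is a comparison of texts plus some arithmetic on coverage and size.

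**1. Does any listed category capture the event?** Take self-injury without suicidal intent and without psychiatric admission.
- SAE list: it is not a death, a psychiatric admission or acute suicidality. Acute aggression is the only candidate. In safety contexts the article links aggression to violence or danger to others ({11b}, {11c}, {22}). Where it means acts against oneself, it says so ({7}, {12}, Table 1 notes). The natural reading is outward.
- AE list: no category names it.
- Unintended effects in {22}: only those related to the interventions, and {20b} states no analysis of them by arm.
- Session forms, as described in {11c}: patients report OAS-M items 1–3 and 7; therapists report suicidality and danger to others. Item 4 is not named.

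**2. How much time does item 4 cover?** Inputs: 2-week recall (Table 1 notes), five post-randomization visits T1 to T5 ({18a}), treatment of 7 to 10 weeks ({11a}), and T5 at 24 weeks after treatment.
- Covered: 5 × 2 = 10 weeks.
- Treatment start to T5: 7 + 24 = 31 to 10 + 24 = 34 weeks.
- Share: 10/34 = 29% to 10/31 = 32%.
- During treatment, only the T1 window can count: at most 2/10 = 20% to 2/7 = 29%.

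**3. How many patients could be involved?** Sample size {14} expects 30% loss: 93 × 0.7 = 65.1, about 65 per arm at T5. The documents give no rate of worsening without acute suicidality or admission, so these shares are assumptions:
- 10%: 65 × 0.10 = 6.5 per arm
- 20%: 65 × 0.20 = 13
- 30%: 65 × 0.30 = 19.5

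A mean contrast can hide such a group. If 13 of 65 rise and 13 fall by the same amount, the mean change is zero.

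**4. What would an item 4 worsening table show by chance?** With no true change and symmetric fluctuation, the share with any increase is (1 − share unchanged)/2.
- Half unchanged: (1 − 0.5)/2 = 25%, or 16 of 65.
- 80% unchanged: (1 − 0.8)/2 = 10%, or 6.5 of 65.

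Patients at zero at T0 can only stay level or rise, so the observed share can be higher. With a threshold in SDs of the tabulated change (normal approximation):
- 1 SD: 16% (about 10 of 65)
- 1.5 SD: 7% (about 4)
- 2 SD: 2% (about 1.5)

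These shares hold only for the SD of the change being tabulated. If the threshold is 1.5 SD of the shorter T-1 to T0 change, and the SD of the longer change is 1.3 or 1.5 times larger (assumption), the cut-off is 1.5/1.3 = 1.15 or 1.5/1.5 = 1.0 SD. The chance share is then about 12% or 16%.

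**5. How precise is the table?** Variance inflation from {14}: 1 + (4 − 1) × 0.075 = 1.225, assuming that the pilot ICC applies to item 4 worsening. Effective size is 65/1.225 = 53.06 per arm. The 95% half-width for the arm difference is 1.96 × √(2p(1 − p)/53.06):
- p = 10%: 11 percentage points
- p = 20%: 15 points
- p = 30%: 17 points

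The table can only be descriptive.

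**The case against.** The strongest reply is that the omission is a defensible choice. Self-injury is a pre-existing feature of the disorder. It is rated by blinded interviewers ({17a}) and will be compared by arm with confidence intervals, so it is reported under outcomes rather than under safety. The Negative Effects Questionnaire is collected as an exploratory outcome. An article also condenses, and the eCRF categories and site instructions are not shown.

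Much of this stands, and it limits the point. It does not remove it: the two lists are worded as definitions, the safety analysis is tied to them, and item 4 is seen only in 2-week windows and as a mean.

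Three stronger readings are tempting, and the documents do not support them.
- A reader might infer that sites will code self-injury as acute aggression in opposite ways. The safety sections favour the outward reading, and site instructions are unseen. The scope is merely unstated.
- A reader might infer that the DSMB cannot see self-injury. Sections {21a} and {23} let it review safety data and accumulated data. What is absent is a stated rule that brings item 4 into a safety report.
- A reader might infer that a blinded item 4 table could serve as the main harms comparison. At about 29% to 32% of the period, and less during treatment, it cannot.

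It is also fair to object that a rise in score is not the same as an omitted event. A patient with frequent but unchanged self-injury is absent from the lists too, and a worsening count would miss that patient.

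**Conclusion.** The point holds in a limited form and is minor. As defined, the AE and SAE lists do not include self-injury, so the harms report by arm can leave out self-injury that involves neither acute suicidality nor psychiatric admission. Item 4 mitigates this only in part.

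The size is unknown. The 6.5 to 19.5 patients per arm rest on assumed worsening shares of 10% to 30% and on 65 patients per arm at T5. The lower part of that range overlaps the 10% to 25% with any increase that symmetric fluctuation alone could produce. Nothing here shows that harm has occurred or is likely to differ between arms. The primary outcome, type I error and power are unaffected.

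**What to change.** **1. Definitions, for remaining groups.** Add to the AE list self-injury that needs medical treatment, irrespective of suicidal intent. State whether acute aggression means outward aggression only. Do not let blinded item 4 scores trigger AE entries, since that would require passing blinded ratings to unblinded staff. Show AE listings before and after the change separately.

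**2. Safety analysis.** Add one descriptive table by arm at each of T1 to T5. It should give the number assessed and the number with item 4 above T0, both for any increase and for an increase of a size fixed before unblinding. State that it covers only the 2-week recall windows. Quote chance shares for the threshold only if it is set from the SD of the change being tabulated.

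**3. DSMB.** Supply that table in a closed report only. The sponsor and central coordinator attend DSMB meetings, item 4 is a secondary outcome, and no interim analysis is planned.

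**Cost.** The table uses data already collected and covers every group. The AE change needs an amendment, one eCRF category and a few more entries. Its capture is prospective only, since enrolment began in May 2024 (Trial status), and it may rest on staff who know the allocation. That is why the listings are split and the table is kept alongside them.
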